### Data analysis

All clinical trial data are collected and managed using REDCap (Research Electronic Data Capture),^48 49^ a web-based electronic case report form designed and hosted by the Norwich Clinical Trials Unit. The platform is designed with audit trails and tracking of data manipulation, with automated export procedures to a range of statistical packages to assist with analysis.

Efficacy of atomoxetine will be assessed following the last patient’s last dose and the ensuing data lock. Differences in the primary efficacy outcome measures will be assessed.

Safety of atomoxetine will be determined by calculating the numbers and percentages of deaths and unique participants with SAEs and AEs leading to discontinuation. Tolerability will be assessed by the review of the list of AEs and reactions (including serious) experienced by participants during the trial.

All data will be stored on the REDCap database, on the servers based at NCTU, apart from imaging and raw data for the Stop/NoGo test. For the Stop/NoGo test, raw data are stored locally, transferred to the lead site and then analysed by the integration method before summary data are transferred to the REDCap database. Imaging data will be transferred in electronic format to the lead site for storage, quality control and quantitative analysis.

Clinical trial data will be analysed at the Norwich Clinical Trials Unit.

Data collected at baseline, that is, visits 1 and 2 before drug administration, including demographics and MRI, will be analysed by members of the study team independently of the clinical trial outcomes. Baseline analyses will focus on advancing scientific understanding of cognitive and behavioural disturbances in PSP, with particular focus on the influence of LC integrity on apathy and impulsivity, captured using 3T and 7T MRI. All study team members collecting data and performing baseline data analysis are blinded to treatment group allocation.

Statistical analyses will be carried out to determine:

An estimate (with inferences) of the effect of atomoxetine on cognition and behaviour, specifically whether atomoxetine is effective in reducing apathy, impulsivity and improving behavioural control.The influence of genetic variations in the NET gene in predicting response to atomoxetine.The influence of CYP2D6 on atomoxetine metabolism (nuisance variable) in predicting response to atomoxetine and in affecting pharmacokinetic measures.Whether volumetric differences in the LC are predictive of atomoxetine response and whether participants with significant behavioural impairments at baseline have significantly different LC volumes than participants with less severe impairments.To develop a predictive model of atomoxetine response by cross-validation, combining clinical and imaging features.^26^

The primary efficacy endpoint will be evaluated by comparing the cognitive and behavioural changes following 8 weeks of daily atomoxetine versus 8 weeks of placebo, as measured by the Apathy-Impulsivity composite subscore from the CBI-R. This subscore includes the following CBI-R subscales: abnormal behaviours (6 items), ‘euphoria’ mood items (2 items), stereotypic and motor behaviours (4 items), eating habits (4 items) and motivation (5 items).^50^,^52^ Owing to this being a crossover trial where participants act as their own control, the effect size is calculated within individuals between treatments (drug and placebo).

The estimate of efficacy will be through a general linear model, with the assumption of normally distributed errors. The model-dependent variable will be the difference in CBI-R between the control period and the intervention period. The model will include recruiting site (as a random effect) and the difference in CBI-R baselines. Other genuine baseline values (ie, where there can be an observable difference between the control and intervention baselines) will be considered for prognostic variables and included in the model. The intercept estimate from the model then serves as the estimate of efficacy. This will be presented with 95% CIs, and a two-sided 5% significance level will be set.

The primary analysis will follow the Intention-to-Treat principle. All participants who complete visit 2 (dose initiation) will be included, as far as data allows, irrespective of actual intervention or dosage received.

Missing values will be dealt with using the following strategy. If the degree of outcome data missing is less than 2.5%, only a complete case analysis will be used. In the case that more than 2.5% and less than 50% of data are missing initially, any missing questionnaire item data will be imputed according to any questionnaire-specific approaches; for example, if one item is missing, the mean of those completed may be used. In the absence of specific guidelines, where individual items are missing, an approach will be discussed and agreed on with the study DMC. When entire questionnaire data are missing, a multiple imputation approach will be used to impute the between-period differences. In the event that more than 50% of the entire questionnaire outcome data are missing, an approach will be discussed and agreed on with the DMC, including, depending on the pattern of missing data, reducing the study to a parallel-arm analysis using first-period data alone.

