### Sample size

A total of 74 participants (37 within each sequence) were estimated a priori to provide 80% power, with statistical significance set at the two-sided 5% level, to detect an effect size of one-third. That is, a difference in mean outcome between treatments of one-third the size of the SD of the individual differences. Given the crossover design, the effect size is calculated within individuals between treatments. A dropout rate of approximately 10–15% is anticipated (based on previous studies in PSP); therefore, the target recruitment is 84 people with PSP (each with an informant). However, the number of patients recruited to the trial may be adjusted according to the actual attrition rate if necessary. Patient participants who are randomised but do not start the treatment phase will be replaced.

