### Current study status

This draft protocol has been aided by the 2013 Standard Protocol Items: Recommendations for Interventional Trials guidelines.^53^

The first participant was randomised on 30 June 2021. Recruitment is expected to take 50 months in total, finishing in autumn 2025.

The course of the trial was interrupted by the COVID-19 pandemic restrictions, and then a temporary pause in trial recruitment related to recurrent IMP supply issues. The study team remained blinded during this period. There were no safety concerns. Later, national supply chain difficulties with commercially available atomoxetine led to intermittent disruptions to recruitment, but no disruption to individual participants’ supply.

As of 16 May 2025, 76 participants have been screened and entered the treatment phase (visit 2) of the study. During the pause for IMP supply issues, 7 participants who initially consented and were randomised in the trial declined or were unable to resume participation in 2023 due to their disease progression or death.

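### The primary crossover model has no period or sequence term, so any period shift that the baseline difference does not absorb costs power and, with unequal sequences, biases the intercept

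*Protocol article*

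**What the plan says.** The Data analysis section of the protocol article sets out the primary efficacy model in four steps.

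- Outcome: "The model-dependent variable will be the difference in CBI-R between the control period and the intervention period".
- Terms: "The model will include recruiting site (as a random effect) and the difference in CBI-R baselines".
- Further terms: "Other genuine baseline values (ie, where there can be an observable difference between the control and intervention baselines) will be considered for prognostic variables".
- Estimator: "The intercept estimate from the model then serves as the estimate of efficacy", and "This will be presented with 95% CIs, and a two-sided 5% significance level will be set".

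Neither this section nor any other part of the article names period or sequence as a term. Treatment order is randomised 1:1 in blocks of 2 or 4 (Blinding section). The Sample size section states: "A total of 74 participants (37 within each sequence) were estimated a priori to provide 80% power", for "a difference in mean outcome between treatments of one-third the size of the SD of the individual differences".

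**The concern.** Fixed characteristics of a participant cancel in a within-person difference, and the rule for further covariates relies on that. Treatment order does not cancel. If scores shift on average between week 8 and week 18, a drug-first participant's control-minus-intervention difference moves by plus that shift and a placebo-first participant's by minus it. Such a shift is plausible: the disease is progressive, and the endpoint is an informant questionnaire, on which habituation or fading expectation could also act.

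The baseline difference (week 0 against week 10) removes only its slope times the shift present in the baselines. A shift that appears only in the outcomes is not removed. The remainder goes into the residual. It drops out of the intercept only when both sequences contribute equal numbers. The primary estimate, its confidence interval and the stated power are all exposed to this.

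**Working it through.** **1. The plan's own figure.** Normal approximation: N = ((1.960 + 0.842)/(1/3))² = 70.6, so 71. With the noncentral t, N = 73 gives 80.2% power and N = 74 gives 80.8%. The stated 74 is reproduced.

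**2. Model.** Let the SD of the difference within a sequence be 1. Write D = θ + s·π + e, with s = +1 for drug-first and −1 for placebo-first, and π the mean change in score from period 1 to period 2. Let the baseline difference have within-sequence SD 1, shift s·π_b, and within-sequence correlation ρ with D. If s is left out (sequences at or near balance):

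- fitted slope b = (ρ + π·π_b)/(1 + π_b²)
- residual shift π_r = π − b·π_b
- residual variance = 1 + π² − (ρ + π·π_b)²/(1 + π_b²)
- bias of the intercept = π_r·(n1 − n2)/(n1 + n2)

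If s is included, the residual variance is 1 − ρ² and the intercept is unbiased.

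**3. Inputs.** From the article: N = 74, θ = 1/3, two-sided 5%. Assumed, because the article gives none of them: π, π_b, ρ and the split after dropout.

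**4. Balanced, 37 v 37, π = 0.5.** SE = √(residual variance/74). Power and type I error are from simulation, 20,000 runs per setting.

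| ρ | π_b | Residual variance without s | SE without / with s | Power without / with s | Type I error without s |
|---|---|---|---|---|---|
| 0 | 0.5 | 1.25 − 0.0625/1.25 = 1.20 | 0.127 / 0.116 | 73.9% / 79.8% | 3.4% |
| 0 | 0 | 1.25 | 0.130 / 0.116 | 72.5% / 79.7% | 2.9% |
| 0.5 | 0.5 | 1.25 − 0.5625/1.25 = 0.80 | 0.104 / 0.101 | 88.6% / 90.0% | 4.6% |
| 0.5 | 0 | 1.25 − 0.25 = 1.00 | 0.116 / 0.101 | 82.8% / 89.7% | 2.5% |

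The intercept's true sampling SD hardly changes. It is the estimated SE that is too large, which is why the test is conservative.

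**5. Smaller shift.** At π = 0.2, balanced and with ρ = 0, power is 79.0% without s and 80.0% with it. With ρ = 0.5 and the same shift in the baselines, it is 90.0% against 90.2%.

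**6. Bias, π = 0.5.** The residual shift is 0.4 for (ρ, π_b) = (0, 0.5), 0.2 for (0.5, 0.5), and 0.5 for either ρ with π_b = 0.

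- 33 v 41: the factor is 8/74 = 0.108. Bias is 0.022 to 0.054 SD. Divided by 1/3, that is 6% to 16% of the target effect.
- 36 v 38: the factor is 2/74 = 0.027. Bias is 0.0054 to 0.0135 SD, or 1.6% to 4.1%.

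The sign reverses if either the shift or the imbalance reverses. In the simulations at 33 v 41, power without s was 57–84% in the unfavourable direction and 84–93% in the favourable one.

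**7. How likely is the extreme split?** Start from 42 v 42 and lose 10 at random (84 to 74). The mean absolute gap is 2.3 people, and a gap of 8 or more has probability 1.5%. A 33 v 41 split therefore mainly represents loss that depends on sequence.

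**8. Cost of the term.** At N = 74, power is 80.77% on 73 df and 80.76% on 72 df.

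**The case against.** **The article condenses a fuller plan.** It says that a detailed statistical analysis plan will be published, and listing some terms does not exclude others, so that plan may contain sequence. This is fair. But the article fixes the outcome, the terms, the estimator and a rule for further covariates, and sequence does not meet that rule. A plan written faithfully from this text would leave it out.

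**The period-specific baseline already guards against drift.** This stands in part. Steady progression between week 0 and week 10 is what that covariate partly captures, and with ρ = 0.5 a shared 0.5 SD shift costs only about one power point. The larger losses need an uninformative covariate or a shift confined to the outcomes, and the article shows neither.

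**The large shifts are speculative.** Also right: 0.5 SD is 1.5 times the effect for which the trial is powered.

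**Participants are retained and missing differences imputed.** The analysis includes all who complete visit 2, people who stop drug are still followed, and missing differences are multiply imputed once more than 2.5% are missing. This lessens any imbalance. It does not remove the problem, because the imputation as described does not name sequence.

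**Stronger readings that the article does not support.** A reader might infer a risk of false positives. With balance the type I error is below 5%, and in simulations at 42 v 32 with shifts up to 1 SD it stayed at or below about 6%. A reader might also take the seven randomised participants who "declined or were unable to resume participation in 2023 due to their disease progression or death" (Current study status) as evidence of unequal sequences. The article does not give their sequence or say that they had started treatment, and those who never start are to be replaced. Nothing documents differential loss by sequence.

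**Conclusion.** The point holds as a should-fix. The stated primary model omits a standard crossover term, and both consequences follow algebraically: inflated residual variance under balance, and bias equal to the residual shift times the relative imbalance otherwise. The size is not known from the article. It is negligible for shifts of 0.2 SD or less with sequences near balance. It reaches about 6 to 7 power points at 0.5 SD when the baseline difference does not absorb the shift. Bias is a few per cent of the target effect under chance imbalance and exceeds 10% only with a large residual shift and a markedly unequal split. These figures rest on the assumed π, π_b, ρ and splits shown above. They do not show that the trial's power claim is wrong or that its result will be biased. They show that the estimator relies on balance, or on a zero residual shift, without need.

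**What to change.** Before unblinding, make three changes.

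1. Add sequence to the primary model, coded +1/2 and −1/2, so that the intercept remains the equally weighted treatment effect. Fitting period and treatment as fixed effects to period-level scores would be an equivalent way of separating the two.
2. Include the same term in the multiple-imputation model for between-period differences.
3. Use it wherever the same difference model is applied to other outcomes. The article specifies that model only for the primary endpoint, so this is a matter of consistency.

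If the statistical analysis plan already contains the term, it is enough to say so in the article's model description. The cost is a sentence or two and one degree of freedom. N = 74 and the 80% power stand, and no new data are needed. Added after unblinding, the same term would be a post hoc choice.

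### The missing-data rule imputes the between-period difference and does not bring in the observed score of a participant who completed only one period; say explicitly that it is used

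*Protocol article*

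**What the plan says.** All of this is in the protocol article.

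- **Outcome (Data analysis).** "The model-dependent variable will be the difference in CBI-R between the control period and the intervention period". Each participant contributes one value.
- **Covariates and estimator (Data analysis).** "The model will include recruiting site (as a random effect) and the difference in CBI-R baselines". Other baseline values that can differ between the two periods may be added. "The intercept estimate from the model then serves as the estimate of efficacy".
- **Analysis set (Data analysis).** "All participants who complete visit 2 (dose initiation) will be included, as far as data allows". A participant with only one completed period therefore belongs to the analysis.
- **Missing data (Data analysis).** "If the degree of outcome data missing is less than 2.5%, only a complete case analysis will be used". Between 2.5% and 50%, single missing items are handled by questionnaire rules, and for whole questionnaires "When entire questionnaire data are missing, a multiple imputation approach will be used to impute the between-period differences". Above 50%, the approach is to be agreed with the data monitoring committee, one option being "reducing the study to a parallel-arm analysis using first-period data alone". This is the only stated use of scores from a single period.
- **Expected loss (Sample size).** "A dropout rate of approximately 10–15% is anticipated (based on previous studies in PSP". The recruitment target is 84.

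**The concern.** In a two-period crossover, someone who leaves between the periods has half of the outcome observed. Once the outcome is defined as a difference, that half disappears from view. The difference is missing, and so is any covariate that is itself a between-period difference. Of the variables named for the analysis model, only site remains.

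If the imputation is built from those variables, it can do little more than redraw differences from the people who completed both periods. The week-8 score, which may be related to why the person left, plays no part. The estimate then relies on dropout being unrelated to the first-period score, or related to it in the same way in both sequences. The second condition is open to doubt. Those who leave after atomoxetine and those who leave after placebo may do so for different reasons, and the Retention section lists adverse events and illness among the grounds for leaving. What is at stake is a modest, avoidable bias in the primary efficacy estimate.

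**Working it through.** **1. The plan's own figure.** Paired design, effect 1/3 SD of the difference, two-sided 5%, 80% power. Normal approximation: n = (1.960 + 0.842)² / (1/3)² = 70.6, so 71. Exact noncentral t: n = 73 (power 0.802); n = 74 gives 0.808. The stated 74 reproduces. The target of 84 implies dropout of 1 − 74/84 = 11.9%, so about 12% is used below.

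**2. Will the rule apply?** 2.5% of 84 is 2.1, so three missing outcomes suffice. The expected loss is 0.10 × 84 = 8.4 to 0.15 × 84 = 12.6, or 8 to 13 people. That is well above the lower threshold and well below 50%.

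**3. Size of the bias if the period-1 score is not used.** Let Y1 and Y2 be the end-of-period scores, with equal variance σ² and correlation ρ. D is control minus intervention, so D = Y2 − Y1 for atomoxetine-first and D = Y1 − Y2 for placebo-first. SD(D) = σ√(2(1 − ρ)). Suppose dropout shifts the mean Y1 of those who remain by δ (in units of σ). Their mean Y2 shifts by ρδ. In units of SD(D), the mean of D then shifts by −δ√((1 − ρ)/2) in atomoxetine-first and by +δ√((1 − ρ)/2) in placebo-first. Averaging the two sequences:

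bias = ½ √((1 − ρ)/2) × (δ_placebo-first − δ_atomoxetine-first)

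Equal shifts cancel; unequal shifts do not.

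Assumptions not in the documents: normal scores; no period or carryover effect; ρ of 0.5 or 0.7; logistic dropout p(Y1) with a log-odds ratio of 1 per SD, higher scores taken as worse. For dropout rate r, δ = −E[Y1 p(Y1)]/(1 − r) for standardised Y1. By numerical integration this is −0.108 at 12%, −0.141 at 16% and −0.074 at 8%. The factor √((1 − ρ)/2) is 0.500 at ρ = 0.5 and 0.387 at ρ = 0.7.

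| Dropout pattern (12% overall) | ρ = 0.5 | ρ = 0.7 |
|---|---|---|
| Same rate and dependence in both sequences | 0 | 0 |
| Same dependence, 16% atomoxetine-first and 8% placebo-first | ½ × 0.500 × 0.067 = +0.017 | ½ × 0.387 × 0.067 = +0.013 |
| Dependence only in atomoxetine-first | ½ × 0.500 × 0.108 = +0.027 | ½ × 0.387 × 0.108 = +0.021 |
| Dependence only in placebo-first | −0.027 | −0.021 |
| Opposite dependence in the two sequences | ½ × 0.500 × 0.216 = +0.054 | ½ × 0.387 × 0.216 = +0.042 |

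Against the design effect of 0.333, the unequal rows run from 0.013 (4%) to 0.054 (16%) in absolute size.

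**4. Check by simulation.** The stated model was fitted (difference regressed on baseline difference, site omitted) with 1,000,000 participants per scenario. At 12% dropout, imputing D without the period-1 score gave:

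- −0.003 to −0.007 with alike dependence (not exactly zero, because the drug effect itself makes the dropout rates differ slightly, for example 10% and 14%);
- about +0.02 to +0.03 with dependence only in atomoxetine-first;
- about −0.025 to −0.034 with dependence only in placebo-first;
- about +0.04 to +0.055 with opposite dependence.

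These agree with complete-case analysis to within about 0.007. A second simulation at about 12% gave estimates of 0.333 to 0.335 with alike dependence, and 0.307 to 0.384 when it differed, against a true 0.333. At 25% dropout, beyond what the plan expects, the largest bias was 0.110.

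**5. With the observed score used.** Imputing D with sequence and the period-1 score as predictors gave a bias between −0.004 and +0.004 in every scenario. The second simulation gave 0.330 to 0.335. The reason is algebraic: given Y1 and sequence, drawing D is the same as drawing Y2 and adding a known shift.

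**The case against.** The strongest reply is that the article names the imputed quantity but not the predictors. A reader might infer that the plan throws away the observed score and that the intention-to-treat estimate is therefore biased. The text does not say so. As step 5 shows, imputing the difference is valid under missing at random if the observed score and sequence are predictors, and a predictor list is commonly left to the statistical analysis plan, which the article promises to publish. This stands, and it rules out calling the rule an error.

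A reader might also infer bias whenever dropout depends on the first-period score. That is too broad: dependence that is alike in both sequences almost cancels. The documents give only an overall dropout rate, with no split by sequence and no timing, so neither the size nor the sign of any bias can be fixed from them.

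Two further points reduce the stakes. Under Retention, people who stop the drug are invited to remain in follow-up, so stopping treatment need not mean missing outcomes. A one-period completer also has many other scales recorded at weeks 0 and 8 that could serve as predictors. Finally, even a bias of 0.05 is less than half the approximate standard error, 1/√74 = 0.116.

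What remains is narrower. The article does fix the difference as the unit of imputation, does not mention the observed component, and assigns single-period scores a role only when more than half the data are missing. Read literally, that points an analyst towards the weaker implementation.

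**Conclusion.** The point holds as a weakness of specification with a conditional consequence. The rule will probably be invoked, since 8 to 13 missing outcomes are expected. If the observed period score is left out, the imputation adds practically nothing to a complete-case analysis. The result is then nearly unbiased when score-dependent dropout is alike in both sequences. When it differs by sequence, the result is off by roughly 0.01 to 0.05 SD of the difference, about 3% to 15% of the design effect, in either direction. The most adverse pattern examined at 12% dropout, opposite dependence at a correlation of 0.5, slightly exceeds that range (0.055, about 17%).

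These sizes rest on assumed correlations of 0.5 to 0.7, an assumed strength of dropout dependence, normal scores and no period or carryover effect. The documents give none of these inputs. It is a cheap improvement to make before the analysis, not a defect that must be repaired for the trial to be interpretable.

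**What to change.** Reword the whole-questionnaire sentence under Data analysis, and carry it into the statistical analysis plan, along these lines: *where an entire CBI-R is missing, composite scores will be multiply imputed at visit level within sequence, using all observed visits (weeks 0, 8, 10, 18 and 22); the outcome and baseline differences will then be formed in each completed data set and the primary model fitted.*

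Either of two alternatives would do the same job:

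- keep the difference as the imputed quantity, but require the observed period scores and sequence as predictors;
- fit a mixed model to the period-level scores with participant as a random effect and treatment and period as fixed effects, using all observed data.

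Reporting the number of one-period completers by sequence would show how much the choice matters. None of these routes protects against dropout that depends on unobserved scores.

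The cost is a sentence and slightly more programming, with no new data or visits. The article places the efficacy analysis after data lock, so the wording should be settled before then, while the team is still blinded.
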